## Abstract

**Background:**

Values are considered central to psychological well-being and mental health, yet the effects of brief interventions targeting valued living remain underexamined. Mobile phone-based delivery may offer a feasible way to implement values-based microinterventions in daily life, while photography may help make values more concrete and accessible. This protocol describes a randomized controlled trial evaluating three values-based microinterventions with and without photography on mental health and values-related outcomes, while also exploring the role of values practice quality as a moderating variable.

**Methods:**

A three-arm, single-blind randomized controlled trial with university students will be conducted. Participants will be randomized to one of three groups: (1) Reading What Matters, a standard written values-based microintervention condition; (2) Capturing What Matters, a photography-supported version of the same microinterventions; or (3) a control group completing only the assessment protocol. Distal outcomes will be assessed at baseline, post-intervention, and two-week follow-up, and will include mental health outcomes, values-related outcomes, and baseline mental imagery ability. Proximal outcomes will be assessed repeatedly through ecological momentary assessments during the intervention period and will include momentary mental health states, momentary valued living processes, and values practice quality.

**Discussion:**

This study will provide initial evidence on the effects of values-based microinterventions on mental health and valued living, the potential contribution of photography, and the role of practice quality in values-focused work.

## Introduction

1

### Values and their role in mental health

1.1

Personal values are those aspects that individuals consider important and meaningful in their lives [1]. In research, values have primarily been conceptualized from two distinct theoretical approaches. First, Schwartz's Theory of Basic Human Values (TBHV; [2]) defines values as beliefs about broad desirable objectives that function as guiding principles for decision-making and behavior. This theory organizes 19 *universal* values in a circular structure based on compatible and conflicting motivations: openness to change, self-enhancement, conservation, and self-transcendence. Second, Acceptance and Commitment Therapy (ACT) positions values as a central construct within the Hexaflex model of psychological flexibility [3]. Within this framework, values are conceptualized as freely chosen, verbally constructed life directions that are expressed through ongoing and evolving patterns of action [4].

While Schwartz's theory focuses on the underlying motivational content of values, ACT focuses on formal processes related to how individuals clarify their values and act in accordance with them in daily life, independently of their specific content, which is known as valued living. Recent research indicates that valued living may be a stronger predictor than the motivational content of values for mental health outcomes [5]. Higher levels of valued living have been associated with lower depressive and anxious symptomatology [6] and with higher levels of well-being and meaning in life [7,8]. Moreover, valued living has been identified as a relevant factor in resilience among university students [7]. Together, these findings support the relevance of situating valued living within a broader model of mental health.

The sustainable mental health framework proposed by Bohlmeijer and Westerhof [9] is particularly useful in this regard, as it conceptualizes mental health not only as the absence of psychological distress but also as the presence of well-being and the capacity to adapt to life challenges over time. From this perspective, mental health is shaped by the interplay between psychological resources (e.g., strengths, positive relationships, and meaning) and psychological barriers (e.g., cognitive biases, dysfunctional beliefs, and avoidance) that either support or hinder adaptation. Within this framework, valued living may function as a psychological resource that provides meaning and direction, thereby supporting individuals’ capacity to adapt to life challenges while maintaining psychological well-being over time. As such, valued living may represent a relevant target for psychological interventions aimed at promoting sustainable mental health.

### Evidence and open questions in values-based interventions

1.2

Values-based interventions (VBIs) are strategies that use personal values as a central component. In the context of mental health, VBIs have mainly focused on promoting valued living by helping individuals clarify what matters to them, identify values-consistent actions, and engage in behavior aligned with those values.

Most research on valued living has been conducted within broader ACT-based interventions that target multiple psychological flexibility processes simultaneously, making it difficult to isolate the specific contribution of values-related processes [10]. However, some studies have isolated valued living as a distinct intervention component. Across these studies, interventions have typically combined reflective exercises to clarify and connect with personally important values, such as psychoeducation and values writing, with more action-oriented exercises aimed at translating values into behavior, such as planning, scheduling, carrying out, and journaling valued actions over time [[11], [12], [13], [14], [15]]. This emerging body of work provides preliminary evidence that VBIs may enhance well-being and reduce psychological distress [14,15], although findings remain mixed [13]. Nevertheless, the evidence base remains limited, and several important questions remain open.

First, many of these studies do not explicitly measure changes in values-related processes, including valued living itself [11,12,14,15], making it difficult to determine whether improvements in mental health are actually driven by changes in valued living. Second, most VBIs have relied on self-guided web-based activities or sessions [[11], [12], [13], [14], [15]]. Such approaches may be less suited to providing immediate, contextually relevant support and to assessing valued living as it unfolds in everyday contexts and fluctuates across moments and days [16]. Therefore, there is a need for research examining whether VBIs delivered in daily life can effectively promote mental health and valued living.

### Microinterventions: A promising strategy to study valued living in daily life

1.3

A promising way to address these open questions is the use of microinterventions, defined as brief, highly targeted strategies designed to have an immediate impact [17,18]. Because microinterventions focus on specific therapeutic components, they may be particularly useful for examining the effects of valued living strategies in isolation, without the confounding influence of broader multi-component interventions. Moreover, their brief format makes them well suited for delivery in daily life. Initial evidence suggests short-term benefits of microinterventions for mental health outcomes [[19], [20], [21]], supporting their potential as brief strategies that can be integrated into daily life.

Digital mental health interventions, particularly smartphone-based interventions, have received increasing attention in recent years [22], as they provide immediate access to strategies and can be integrated into users' daily lives. In this context, mobile phones represent an ideal channel for delivering microinterventions in individuals’ natural contexts. When microinterventions are delivered at fixed or on-demand times via mobile devices, they are referred to as ecological momentary interventions (EMIs; [23,24]). Mobile phones also enable the collection of ecological momentary assessments (EMAs), which provide real-time measurement of outcomes in daily-life contexts. Meta-analyses have shown their effectiveness in improving mental health [[25], [26], [27]], with small effects on well-being and common symptomatology and moderate effects on emotion regulation [28]. In university students, mobile phone-based interventions have also been shown to reduce symptomatology and risky behaviors, such as alcohol and tobacco use [29,30]. However, mobile phone-based microinterventions specifically targeting valued living as a stand-alone intervention component have received limited attention. This highlights the need to examine values-based microinterventions delivered in daily-life contexts.

### Factors that may influence the effects of microinterventions

1.4

#### The role of photography

1.4.1

A key difficulty when targeting values is their abstract and often ambiguous nature [31,32], which may pose challenges for accessing and contacting them. Moreover, this challenge may be even greater in the context of microinterventions, where the time available to engage with personal values is limited. Therefore, strategies that facilitate access to values may be particularly important in this context.

Photography may serve as a promising medium for enhancing values-based microinterventions by transforming abstract values into concrete, personally meaningful visual cues [33]. Through photography-based tasks, such as creating and repeatedly observing participant-produced photographs, individuals may represent their values through specific images, people, places, or moments. These photographs may function as reminders that reactivate associated values when viewed directly, while similar cues encountered in everyday life may also trigger value-related thoughts. For example, if a participant represents the value of “being creative” with a photograph of their guitar, later seeing that instrument at home or elsewhere may serve as a reminder of this value. In this way, photographs may increase the concreteness, salience, and accessibility of personal values, making them more likely to come to mind spontaneously.

Beyond making values more concrete and accessible, observing photographs may also activate broader networks of memories, thoughts, emotions, and mental images associated with personally important values. For instance, viewing the photograph of the guitar may also evoke memories of playing music, feelings of inspiration or enjoyment, thoughts about self-expression, or experiences in which the individual felt engaged or fulfilled. In this way, photographs may provide faster and more direct access to value-related affective states, such as meaning or vitality. In line with this, research has shown that both taking and reviewing photographs can positively influence mood and affect [[34], [35], [36]], facilitate emotion regulation [37], and elicit feelings of meaning in values-focused work [38]. Consistent with broaden-and-build theory [39], these positive and meaningful experiences may broaden individuals’ momentary thought-action repertoires, facilitating additional thoughts, memories, associations, feelings, and value-congruent actions.

Moreover, participant-produced photography may enhance the appeal of values-based microinterventions by increasing personal relevance and a sense of ownership over the intervention content. Because the images are self-generated and connected to the participant's own life, the intervention may feel more personally meaningful and engaging, thereby potentially improving adherence. However, the extent to which participant-produced photography improves the effects of values-based microinterventions remains to be empirically examined.

#### The role of quality of practice

1.4.2

Another important aspect of VBIs, and of psychological interventions more broadly, is the quality of practice. This refers not only to the content addressed during practice, but also to how effectively that content is implemented [40]. Practice quality has been extensively examined in interventions that rely primarily on meditation, imagination, and visualization, such as those derived from compassion-based traditions [41]. Within this literature, practice quality has often been operationalized through two dimensions: Mental Imagery Ability (MIA) and somatosensory properties [42]. MIA refers to the cognitive processes involved in creating, maintaining, examining, and manipulating mental representations ([43], as cited in Ref. [42]). Somatosensory properties, in turn, refer to the bodily sensations that accompany these experiences.

Similar to compassion-focused approaches, many VBIs designed to foster values clarification involve visualization- and imagination-based strategies. For instance, the “Sweet Spot” exercise invites individuals to recall past meaningful moments and identify the values expressed in those experiences [44]. Other values exercises use future-oriented scenarios, such as “Attending Your Own Funeral”, in which participants imagine their own funeral and reflect on what they would want significant others to say about the life they had lived and the values they had embodied [45]. These exercises suggest that the quality of values practice may depend, at least in part, on the ability to generate and engage with mental imagery.

At the same time, values work may also involve somatosensory and affective components, as LeJeune and Luoma [46] suggest that working with values in therapy often evokes emotional and physical responses. Luoma et al. [47] further describe vitality as a dynamic, vibrant quality that often emerges when individuals deeply connect with their values. Similarly, Barney et al. [48] emphasize that valuing experiences can elicit feelings of vitality and meaningfulness.

Thus, MIA and somatosensory engagement may provide a useful starting point for investigating the quality of values practice. Understanding these internal dimensions is crucial for clarifying the mechanisms through which VBIs achieve their effects. When values practice is supported by stronger mental imagery and somatosensory engagement, individuals may experience a deeper connection with their values and, consequently, greater valued living. This deeper valued living, in turn, is expected to amplify positive effects across dimensions of sustainable mental health. However, few studies have examined the role of practice quality in values-focused work.

### Objectives and hypothesis

1.5

Based on the literature reviewed above, this study aims to:(1)Examine the effects of three mobile phone-based microinterventions targeting valued living on mental health and values-related outcomes over one week. Specifically, we aim to investigate effects at three temporal levels: (1.a) proximal effects (immediate changes following each microintervention), (1.b) trajectory effects (changes across days associated with repeated microintervention use), and (1.c) distal effects (changes observed after the intervention period and at the two-week follow-up).(2)Examine whether photography-supported microinterventions enhance the effects referred to in the first objective compared to non-photography-supported microinterventions.(3)Explore the moderating role of baseline MIA and momentary quality of values practice on the effects of the microinterventions.

We formulate the following hypotheses:Hypothesis 1The three values-based microinterventions will show positive effects on mental health and values-related outcomes across the three temporal levels: (i.e., proximal, trajectory and distal effects).Hypothesis 2Photography-supported microinterventions will enhance the effects referred to in Hypothesis 1 compared to non-photography-supported microinterventions across all three temporal levels.Hypothesis 3Higher baseline MIA and higher quality of values practice will be associated with stronger microintervention effects referred to in Hypothesis 1 across the three temporal levels.

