**Fig. 2 fig2:**
[figure not shown]
Schedule of microinterventions. Abbreviations: FR: Friendly reminder

The 50th birthday party microintervention will be sent on the first day after downloading the app, and it will be sent only once with the following message: “It's time to start the journey! Listen to your first visualization”*.* When participants enter the app, this module will be named “Starting your journey!” and will remain available for the next 24 h. Throughout the day, participants will receive two reminders if the strategy has not been completed. The first reminder will be sent at 3:00 p.m. with the message: “Don't forget your first notification! It's really important to us that you complete it”. The second reminder will be sent at 9:00 p.m. with the message: “To stay in the study, please complete today's notification. We'd love to keep you on board!”

The 3-min wake-up microintervention will be sent daily in the morning during the 6 days following the initial microintervention, with the message: “Time for a quick exercise! It will disappear at 12:00 p.m.” When participants enter the app, this module will be named “Before starting your day!” and will be available from 6:00 a.m. to 12:00 p.m. Reminders will be sent at 9:00 a.m. and at 11:00 a.m. with the following messages, respectively: “Don't miss your morning check-in! It takes less than 5 min – Available until 12:00!” and “Don't forget about me! Morning notification disappears in 1 h”

The friendly reminder microintervention will be sent three times per day and will be available from 3:00 p.m. to 5:00 p.m., from 6:00 p.m. to 8:00 p.m., and from 9:00 p.m. to 11:00 p.m., on the same days as the morning notifications They will appear with the message: “Just 1 question”.

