#### Quality of values practice

2.10.3

The quality of values practice will be measured after the 50th birthday party with the Values Practice Quality Scale (VPQS). Considering that compassion and values-based practices share common elements, such as the use of imagery and bodily sensations, we adapted the Compassion Practice Quality Scale (CPQS) by Navarrete et al. [42] and constructed the VPQS, particularly for this study. The adapted VPQS was based on values literature and incorporates expressions specifically aligned with the values process, ensuring greater relevance and applicability. This 10-item scale measures the values practice quality with two subscales: imagery (items 1,2,3,4,6, and 8), e.g., “During the exercise, I had a lot of difficulty choosing the elements that made up the mental scene) and somatic (items 5,7,9, and 10) e.g., “During the exercise, I noticed feelings of vitality and expansion in my body”. Items are rated on a scale from 0 to 100, indicating the percentage of time their experience aligns with each statement. Higher scores indicate better practice quality (fewer difficulties), except for negative items (items 1, 2, 3, 4, 6, and 8). CPQS has good reliability and validity in its version in Spanish [42]. Reliability and validity of the VPQS remains to be tested. A short 4-item daily questionnaire for assessing the quality of values practice after the 3-min wake-up will be created by selecting the items with the highest factor loadings from the original scale.

Table 2 provides an overview of the proximal outcomes.

**Table 2 tbl2:** Study variables, EMA items and assessment time points.

Variable	EMA items	50th birthday party		3-min wake-up		Friendly reminder
		Pre	Post	Pre	Post	Pre
Well-being	At this moment, what is your level of well-being?	x	x	x	x	-
	How happy do you feel right now?	x	x	x	x	-
	At this moment, to what extent are you satisfied with your life?	x	x	x	x	-
	At this moment, to what extent are you feeling that your life has a sense of direction or meaning to it?	x	x	x	x	-
Depression	At this moment, to what extent are you feeling little interest or pleasure in doing things?	x	x	x	x	-
	At this moment, to what extent are you feeling down, depressed or hopeless?	x	x	x	x	-
Anxiety	At this moment, to what extent are you feeling nervous, anxious, or on edge?	x	x	x	x	-
	At this moment, to what extent are you not being able to stop or control worrying?	x	x	x	x	-

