### Statistical analysis

2.11

Data will be processed and analyzed with R 4.4.2 [66] or newer and the RStudio interface [67].

First, to test proximal and trajectory effects with and without photography, as well as the moderating role of quality of practice (Objectives 1.a, 1.b, 2, and 3), linear mixed-effects models will be fitted using the *lmerTest* package [68]. Separate models will be fitted for each proximal outcome within each microintervention as the dependent variables. For the 50th birthday party microintervention, participants from the RWM and CWM conditions will be pooled for the pre-post analysis, as the photography component in the CWM condition is introduced only after the post-microintervention EMA. Thus, time (pre- vs. post-microintervention), quality of practice, and their interaction will be entered as fixed-effect predictors. For values awareness, frequency of valued actions and awareness during valued actions, which require time and opportunity to occur or be noticed in daily life, change will be examined using the next available EMA assessment, collected the following day before the 3-min wake-up microintervention. Given that this assessment occurs after the photography task, models including condition will be conducted to examine potential RWM-CWM differences. For the 3-min wake-up microintervention, condition (RWM, CWM), time (pre- vs. post-microintervention), day (from 1 to 6), quality of practice, and their interactions will be entered as fixed-effect predictors. For the friendly reminder microintervention, condition (RWM, CWM, control), time (pre- vs. post-microintervention), day (from 1 to 6), quality of practice, and their interactions will be entered as fixed-effect predictors. Additionally, to examine the combined effect of the 3-min wake-up and friendly reminder microinterventions across the intervention period, linear mixed-effects models will be fitted using the variables assessed in the first EMA assessment of each day as dependent variables. This approach will allow us to examine whether values awareness, frequency of valued actions and awareness during valued actions change across repeated daily engagement with the intervention. Condition (RWM, CWM, control), day (from 1 to 6), and their interaction will be entered as fixed-effect predictors. Participant will be entered as a random-effect predictor in all models. Models will be estimated using restricted maximum likelihood (REML). Under the missing at random (MAR) assumption, all available data will be used, so participants with incomplete EMA data will still contribute to the analyses based on the observations they provide.

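### The wake-up model lists a single quality-of-practice term, so its time-by-quality interaction mixes day-to-day quality with stable differences between people and does not isolate the momentary moderation that Objective 3 asks about

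*Protocol article*

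**What the plan says.** Section 1.5 of the protocol article sets two moderators side by side, a baseline trait and an EMA measure: "Explore the moderating role of baseline MIA and momentary quality of values practice on the effects of the microinterventions". Hypothesis 3, in the same section, drops the word momentary. It predicts only that higher baseline mental imagery ability (MIA) and higher practice quality go together with stronger effects.

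Section 2.7 says the wake-up "will be sent daily in the morning during the 6 days following the initial microintervention". Section 2.10.3 adds that "A short 4-item daily questionnaire for assessing the quality of values practice after the 3-min wake-up will be created", and on the response format: "Items are rated on a scale from 0 to 100, indicating the percentage of time their experience aligns with each statement". Table 2 places these items in the post-exercise column, alongside the post EMA outcomes.

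For the wake-up model, section 2.11 lists "condition (RWM, CWM), time (pre- vs. post-microintervention), day (from 1 to 6), quality of practice, and their interactions will be entered as fixed-effect predictors", and then: "Participant will be entered as a random-effect predictor in all models". It mentions no person mean, no daily deviation and no centring. Baseline MIA is not in this model; it appears only as a conditional covariate in the distal ANOVA.

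**The concern.** A rating repeated over several days carries two kinds of information: how well a person usually practises, and whether a given day's practice was better or worse than usual for that person. A momentary moderator is the second kind. A single term forces one slope on both.

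People who imagine easily, are enthusiastic, or rate generously on 0 to 100 scales may report both higher quality and larger pre-post changes on every day. That alone can make time-by-quality significant, even if a better-than-usual practice is not followed by a larger change. Conversely, a real day-to-day association is diluted by between-person variation that carries no signal.

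The between-person link is plausible on the protocol's own reasoning. Section 1.4.2 suggests that practice quality may depend partly on imagery ability, and Hypothesis 3 expects imagery ability to go with stronger effects. At stake is which sentence the results paper may write: that the quality of a given practice goes with its effect, or that certain people report both.

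**Working it through.** **Inputs.** From the protocol: 159 participants allocated 1:1:1, so 159 × 2/3 = 106 in the two active arms; 6 wake-up days; pre and post ratings; one quality term; a participant random effect; REML. The protocol gives no ICC for quality, no quality-response link and no variances, so there is no planned figure to reproduce on this point.

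**What the single term estimates.** Write the pre-post change of person i on day j as

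change = a + βB × (person's usual quality) + βW × (that day's deviation from it) + error.

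Regressing change on the undivided rating gives a slope of approximately

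ICC × βB + (1 − ICC) × βW.

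A participant random intercept does not remove the βB part. It absorbs differences in level, and these cancel in the post-minus-pre difference.

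**Simulation A.** 106 people, 6 days, 75% of days completed, 150 runs per setting, random-intercept REML fit, interactions limited to time with quality, condition and day. Assumed: quality SD 20; outcome SDs 15 (person), 8 (occasion) and 8 (residual); mean change 4 points; βW = 0. At ICC 0.5 the between-person SD of quality is 20 × √0.5 = 14.1, so βB = 0.1 or 0.2 means 1.4 or 2.8 points more change per SD of usual quality.

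| ICC | βB | Slope by formula | Simulated slope | Single term significant | Daily deviation significant |
|---|---|---|---|---|---|
| 0.3 | 0.1 | 0.03 | 0.033 | 11% | 1% |
| 0.3 | 0.2 | 0.06 | 0.062 | 37% | 1% |
| 0.5 | 0.1 | 0.05 | 0.052 | 25% | 1% |
| 0.5 | 0.2 | 0.10 | 0.101 | 86% | 1% |
| 0.7 | 0.1 | 0.07 | 0.072 | 53% | 1% |
| 0.7 | 0.2 | 0.14 | 0.141 | 99% | 1% |

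With βB = 0.05 the single term was significant in 5% (ICC 0.3) and 7% (ICC 0.5) of runs. With no association at either level it was significant in about 1%. The null rates lie below 5% because a participant intercept alone leaves the shared day-level component in the error: the model takes the variance of a pre-post difference as about 2 × (64 + 64) = 256, while the true value is 2 × 64 = 128. This affects both tests alike.

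**Dilution.** With βW = 0.1, βB = 0 and ICC 0.5, the formula gives 0.5 × 0.1 = 0.05. The single term averaged 0.054 and was significant in 23% of runs; the daily deviation averaged 0.104 and was significant in 45%.

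**Simulation B, other assumptions.** 106 people, 5 completed days, 250 runs per setting, standardised quality, person-level response SD 0.3, no day-to-day moderation. With a correlation of 0.3 between usual quality and response, the single term was significant in 27% (ICC 0.4) and 40% (ICC 0.6) of runs; with a correlation of 0.5, in 64% and 83%. The person-centred test stayed at or below 2%. Adding a random time slope left 20–38% and 57–80%, so it is no cure. With no link at either level the single term was significant in 2.8–5.6%. With only a day-to-day effect of 0.12, the formula gives 0.6 × 0.12 = 0.072 and 0.4 × 0.12 = 0.048. The simulated estimates were 0.07 and 0.05, and power fell from 59% to 43% and from 35% to 22%.

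**The case against.** The strongest reply is that the protocol never promises a within-person test. In this article momentary is mainly a label for EMA measurement, and some items under that label look back 24 hours. Quality is also rated once after the birthday exercise and used as a moderator there, where no within-person test is possible. The rationale, "When values practice is supported by stronger mental imagery and somatosensory engagement, individuals may experience a deeper connection with their values", fits differences between people as well as differences between days. Imagery ability is part of how the protocol understands practice quality, so it is not simply contamination. Section 2.11 says neither raw nor centred, and an article may leave centring to a fuller plan. The simulations also omit the higher-order interactions in the listed model.

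Much of this stands. A reader might infer that the model would falsely confirm Hypothesis 3. The text does not support that, because a between-person link satisfies the hypothesis as worded. A reader might also infer that the raw score is definitely entered; the article does not say so.

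What does not stand is treating the split as a mere scaling detail. Separating the two components takes two quality terms, and section 2.11 lists one. Objective 3 sets the EMA-based moderator apart from baseline MIA, and daily ratings are collected, so a reader will take a significant interaction as a statement about practice on the day unless told otherwise.

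**Conclusion.** The point holds as a matter of interpretation. As listed, the wake-up model's time-by-quality coefficient is a weighted mix of between-person and day-to-day associations. It can be significant with no day-to-day association, provided people with generally higher quality also report larger changes, and it can dilute a day-to-day association that is real.

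The direction follows from the model. The size does not: the 11% to 99% range depends on the assumed ICC and between-person link and on a simplified set of interactions, with simulation error of up to about 4 percentage points (√(0.5 × 0.5 / 150) = 0.041). These are not error rates for Hypothesis 3, and without a link at either level there is no excess.

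One further inference should be resisted. Quality is rated together with the post EMA, so even a clean daily term could reflect mood just after the exercise. The split shows a within-person association, not influence. As the objective is exploratory, this is an inexpensive improvement that should be made; it does not threaten the trial.

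**What to change.** In the wake-up model of section 2.11, replace the single quality term with two: the participant's mean quality over completed wake-ups, centred at the grand mean, and the daily deviation from that participant's mean. Interact each with time, and add higher-order interactions with condition and day only where a stated question needs them. Name time by daily deviation as the term for the momentary part of Objective 3. Report time by person mean separately, as a between-person association beside MIA. State that the birthday rating, given once, supports only a between-person association, and that the daily term is an association because quality is rated with the post EMA.

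The cost is two derived variables and no new data. With time interactions only, two quality coefficients (quality, time by quality) become four. Crossing everything would be dearer: with linear day, 2 × 2 × 2 × 2 = 16 fixed effects become 2 × 2 × 2 × 3 = 24; with day as six categories, 2 × 2 × 6 × 2 = 48 become 2 × 2 × 6 × 3 = 72. That is why the higher-order terms should be limited. The momentary test will also use only the within-person share of the quality variance, so a purely between-person association no longer counts towards it.
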